## Background

Major depressive disorder (MDD) is one of the most prevalent psychiatric disorders characterized by high relapse and/or recurrence rates. Relapse is defined as ‘a return of symptoms satisfying the full syndrome criteria for an episode that occurs during the period of remission, but before recovery’, where remission is a period in which the individual no longer meets syndrome criteria for the disorder and has no more than minimal symptoms, and recovery is being in remission for 6 months or longer; recurrence is ’ the appearance of a new episode of MDD occurring during recovery’ [1]. In a large prospective study, a recurrence rate of 85% was observed in outpatients with MDD during a follow-up period of 15 years [2]. Furthermore, the recurrence risk has been shown to increase with 16% after each successive episode [3]. Given the high psychological as well as social and economic burden associated with MDD, relapse/recurrence prevention is extremely important. The most commonly used strategy to prevent relapse/recurrence is maintenance treatment with antidepressant medication (mADM). International guidelines recommend that patients with recurrent MDD should continue mADM for at least two years after remission [4]. A meta-analysis showed that mADM reduces relapse/recurrence rates significantly compared to placebo (18% versus 41%) based on 31 randomized controlled trials with follow-up periods ranging from 6 to 36 months [5]. However, despite the established effectiveness of mADM as a preventive strategy, it has several disadvantages. First, many patients are unwilling to continue mADM for a longer period [6] and adherence is typically low [7]. Second, many patients experience disturbing side effects [8]. Moreover, many patients prefer psychological over pharmacological treatment [9]. Psychotherapeutic approaches also seem to have long-term beneficial effects, whereas effects of mADM cease after discontinuation [10]. To address the need for psychological interventions targeting relapse prevention, Segal, Williams and Teasdale developed Mindfulness-Based Cognitive Therapy (MBCT) [11]. The aim of MBCT is not to change or eliminate depressive symptoms, but rather to relate to them in a different way, i.e. with a more accepting, mild attitude. The rationale behind the MBCT program is based on an empirically supported, theoretical framework suggesting that patients with recurrent depression become more vulnerable to developing depression as cognitive reactivity increases (for a review see [12]). Cognitive reactivity refers to negative modes of thinking and behaving that are reactivated in periods of stress or low mood. It is suggested that these (automatic) negative reactions in turn, lead to a further lowering of mood, eventually turning into a depressive relapse/recurrence [13]. Cognitive reactivity is strongly related to rumination, which refers to recurrently thinking about one’s depressive symptoms and their possible causes and implications. Rumination is thought to be an important cognitive vulnerability factor for both onset and relapse/recurrence in depression [14,15]. MBCT is targeted at recognizing these cognitive and behavioral reactions to low mood or other stressful situations, and to observe these reactions with acceptance and kindness and from a wider, decentered perspective. Indeed, there is evidence that MBCT diminishes the ‘toxic’ relationship between post-treatment cognitive reactivity and depressive relapse [16] and that decreased rumination mediates the effects of MBCT [17]. Unlike cognitive reactivity and rumination, self-compassion seems to be a beneficial factor that is protective against depression. Self-compassion can be described as a combination of (a) self-kindness - being kind and understanding toward oneself in instances of pain or failure, (b) common humanity - perceiving one’s experiences as part of the larger human experience, and (c) mindfulness - holding painful thoughts and feelings in balanced awareness [18]. Evidence suggests that both self-compassion and mindfulness skills mediate the effect of MBCT on relapse/recurrence [16]. Three randomized controlled trials (RCTs) have shown that MBCT in addition to treatment as usual (TAU) significantly reduced the relapse/recurrence risk compared with TAU alone, over a period of 14 months [19-21]. In the first two trials [19,20], beneficial effects of MBCT were seen in patients with three or more past episodes, whereas no difference in relapse/recurrence percentages between MBCT and TAU was observed in patients with two past episodes (but see [22] for positive effects of MBCT in patients with one or two past episodes). Another trial has shown that MBCT’s prophylactic effect is at least equal to mADM for patients with three or more past episodes [23]. This latter finding may specifically apply to patients whose remission is unstable [24]. There is also evidence that MBCT might reduce subthreshold depressive symptoms, an important risk factor for relapse/recurrence, in patients remitted from MDD [22] and patients with current MDD [17]. A recent meta-analysis [25] showed that the overall risk ratio for relapse/recurrence after MBCT is 0.66 (a relative risk reduction of 34%) compared with TAU or placebo indicating that MBCT is indeed an effective prophylactic intervention for patients with recurrent MDD in remission. However, the prophylactic effectiveness of the *combination* of MBCT plus mADM has not yet been compared with either mADM or MBCT on their own. More specifically, MBCT has not been studied as an additional treatment in patients continuing mADM, rather than TAU, to prevent relapse/recurrence. Also, up to now we do not know if continuing mADM after MBCT has additional benefits over withdrawing from mADM after MBCT. As more and more MBCT courses are available, answering these specific questions becomes increasingly important for patients and clinicians in order to find the optimal strategy to prevent relapse/recurrence. The current study is designed to answer these questions.

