#### Process data

*Adherence to MBCT and adherence to mADM* is assessed during the entire study period using a calendar on which patients register on a daily basis their adherence to mindfulness exercises formal, informal, or none - and their adherence to mADM - full adherence, partial adherence (e.g. lower dosage than prescribed), or no adherence. This information is combined with the 4-item Morisky Medication Adherence Scale (MMAS [44]) with scores ranging from 0 (perfect adherence) to 4 (low adherence). *Rumination* is measured with the extended version of the Ruminative Response Scale (RRS-EXT [45]). The RRS-EXT enables distinction between ‘reflection’ and ‘brooding’, the former referring to a more adaptive, and the latter to a more maladaptive way of thinking about depression. *Cognitive reactivity* is assessed using the Leiden Index of Depression Sensitivity – Revised (LEIDS-R [46]). This scale consists of six subscales: hopelessness/suicidality, acceptance/coping, aggression, control/perfectionism, risk aversion, and rumination. To examine *mindfulness skills*, we administer the Dutch Five Facet Mindfulness Questionnaire (FFMQ [47]). The scale consists of 39 items divided into the subscales observing, describing, acting with awareness, nonjudging and nonreactivity. *Self- compassion* is measured with the Self Compassion Scale (SCS [48]). The SCS has 26 items measuring three concepts that are related to self-compassion: a) self-kindness versus self-judgment, b) common humanity versus isolation, and c) mindfulness versus over-identification. *Daily attention*. The Mindful Attention Awareness Scale (MAAS [49]) is administered before each MBCT session to assess mindful attention in daily life. *Positive and negative affect* is assessed before each MBCT session using the International Positive and Negative Affect Scale - Short Form (I-PANAS-SF [50]).

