##### Mechanisms of change

Mediation analyses will be used to investigate the possible underlying mechanisms of change in MBCT. In accordance with other trials, these analyses will only include patients who have received an ‘adequate dose’ of MBCT, which is defined as participation in ≥ 4 of 8 MBCT sessions [16,19]. In this subsample, we will test the mediating effect of adherence to MBCT, rumination, cognitive reactivity, mindfulness skills, and self-compassion, on depressive relapse/recurrence and depression severity as outcomes, using a multiple mediation model following the approach suggested by Preacher and Hayes [57]. In addition, we will use Hierarchical Linear Modeling techniques to investigate whether change in daily attention/awareness causally influences positive and negative effect. We will perform multilevel mediational analyses following the procedure reported by Kenny, Korchmaros & Bolger [58]. We will ‘lag’ the mediator variable (daily attention/awareness) by examining whether changes on the MAAS at time *t-1* account for changes in the outcome variable (i.e. positive and negative affect) at time *t* for every MBCT session.

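### The session-level analysis asks a causal question but tests only attention-to-affect, in uncontrolled series, so mood driving attention could distort the result or pass for an MBCT mechanism

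*Protocol article*

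**What the plan says.** The protocol article, Mechanisms of change, opens with the purpose: "Mediation analyses will be used to investigate the possible underlying mechanisms of change in MBCT". It then adds a session-level multilevel analysis to examine whether "change in daily attention/awareness causally influences positive and negative effect" (the last word is evidently a slip for affect). The test is given as whether "changes on the MAAS at time *t-1* account for changes in the outcome variable" at time t. No model in the other direction, no adjustment for earlier affect and no caution about a causal reading is stated.

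Under Process data, the MAAS "is administered before each MBCT session to assess mindful attention in daily life", and affect "is assessed before each MBCT session using the International Positive and Negative Affect Scale" in its short form. Table 1 lists both scales only in the MBCT column. The section also limits the mediation analyses to patients who attended at least 4 of the 8 sessions.

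The Background describes cognitive reactivity as "negative modes of thinking and behaving that are reactivated in periods of stress or low mood", and adds that these reactions lower mood further.

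**The concern.** The causal question has only the time lag to rest on. Patients on mADM alone provide no MAAS or affect series, and the patients analysed are those who attended, so there is no randomised contrast behind the session-level association. A lag shows that one measurement came before another. It does not rule out that earlier mood shaped both the earlier attention score and the later mood.

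Mood persists from week to week. If mood moves attention, last week's MAAS carries information about last week's mood, and so about this week's mood, even if attention does nothing. At stake is what the trial may say about how MBCT works: feedback from mood could be mistaken for a mechanism, or could bias the estimate the other way.

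**Working it through.** The plan gives no sample size, power or effect for this analysis, so there is no figure to reproduce. The check asks what the one-directional test shows when the true attention-to-affect effect is zero.

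**Inputs from the protocol article**
- Eight weekly sessions, both scales before each.
- Planned MBCT recipients: 48 (trial 1, combination arm) + 2 × 140 (trial 2, both arms) = 328. This is an upper bound, because the analysis is limited to attenders, so n = 100 is also shown.

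**Assumptions (none from the documents)**
- Affect: A(t) = 0.5·A(t-1) + error, scored so that higher is better.
- Attention: M(t) = 0.3·M(t-1) + 0.3·A(t) + error (same-session reverse effect), or with A(t-1) in place of A(t) (lag-1 reverse effect).
- Both observed with reliability 0.75, i.e. error variance 0.25/0.75 = one third of the true variance.
- 400 runs. Pooled regression with patient-clustered errors stands in for the multilevel model.

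**Why the sign depends on the model.** Let φ be the autocorrelation of affect. Take the same-session case, where attention mirrors current mood.
- Levels: corr(A(t), A(t-1)) = φ = 0.5. Earlier MAAS therefore predicts later affect positively.
- Changes: corr(ΔA(t), ΔA(t-1)) = -(1 - φ)/2 = -(1 - 0.5)/2 = -0.25. A rise tends to be followed by a fall, so earlier MAAS change predicts later affect change negatively. With φ = 0.8 this is -(1 - 0.8)/2 = -0.10.

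Measurement error and MAAS persistence alter these values, but the signs agree with the simulation.

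**Results (true forward effect zero)**

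| Model | n = 328 | n = 100 |
|---|---|---|
| Lagged MAAS level, no prior affect: significant, beneficial | 100% (same-session), 85% (lag-1) | 91%, 37% |
| Same, adjusted for prior affect | about 44%, about 12% | about 7-15% |
| Mirrored model (affect at t-1 to MAAS at t): true path detected | 100% | 95-100% |
| Literal change on lagged change: significant, beneficial | about 0% | 0-1% |

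In the literal change model, significant results of the wrong sign appeared in about 8-48% of runs across these settings. With 400 runs, a rate near 50% has a standard error of √(0.5 × 0.5/400) = 2.5 percentage points. At n = 328 the mirrored model had the larger test statistic in every run.

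The excess in the adjusted forward model comes from measurement error: at reliability 1.0 its rate falls to 3.5-3.8%.

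**Sensitivity, with other assumed parameters** (mood-to-attention slope 0.4, or 0.2 same-session plus 0.3 lagged; φ 0.5 or 0.8)
- The literal change model again gave 0-1% beneficial results under autoregressive mood, with wrong-sign results in 8-93% of runs.
- If changes in mood instead carry momentum into the next week, the same model gave false beneficial results in 62% (n = 100) to 98% (n = 328).
- Adjusted for prior affect, the forward path on levels was falsely beneficial in about 2-4% when mood acts within the session. It was 12% (n = 100) to 33% (n = 328) when mood also acts with a lag and person-level differences are not modelled.

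**The case against.** The strongest objection is that the high false-positive rates belong to a model the article does not describe. Its wording is changes on lagged changes, and for that model a false beneficial result is close to absent under autoregressive mood. This stands. A reader might infer that mood driving attention *would* be reported as an MBCT mechanism, or that the plan as written has an 85-100% false-positive rate. The documents support neither: the first should be *could*, and the second applies only to lagged levels without prior affect at n = 328.

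A reader might also infer that the Background itself describes mood driving attention. It does not. It describes a loop between mood and negative thinking, including the direction from thinking to mood, and does not name attention. Cognitive reactivity and rumination have their own scales. The loop makes feedback plausible and no more.

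Nor does the plan assert causation: it asks a question, under a heading about possible mechanisms, and the lag does give temporal order. It also relies on a cited multilevel procedure that is not at hand, and an article may leave covariates and supplementary models to a fuller document. That is fair as to omitted detail. But the article itself states the causal wording, the single direction and the setting without a control series, and these do not fit together whatever else is specified.

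Finally, a mirrored model does not repair the forward test, as the adjusted rates show. This also stands, and it limits what may be concluded from the pair.

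**Conclusion.** The point holds in a limited form. A causal question is tied to a test in one direction, in series with no untreated comparison, and that test cannot tell attention leading affect from affect leading attention. If mood drives attention, the result is distorted under either reading of the model: false beneficial findings in about 37-100% of runs with lagged levels and no prior affect, and significant wrong-sign findings in about 8-48% with changes on lagged changes at reliability 0.75. Beneficial false positives in the change model need an extra assumption, such as momentum in mood.

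All these sizes rest on assumed persistence, effect and reliability, and on a simple stand-in for the multilevel model. They show that distortion is possible and that its sign varies; they do not predict this trial's result. The matter is minor: a secondary mechanism analysis, with the relapse/recurrence comparison in each trial unaffected.

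**What to change.** 1. From the same session records, add the mirrored model: affect at t-1 predicting MAAS at t.
2. Adjust each model for its own outcome at t-1 and for session number, and report the two paths side by side.
3. Do not conclude that attention leads affect because the forward path is significant. Judge it against the reverse path, and state that measurement error can leave a spurious forward path even after adjustment.
4. Replace *causally influences* with *precedes* or *predicts*, and correct the slip of effect for affect.

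The cost is one more model on data already planned, and a more cautious claim. No new measurement or patient is needed.

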##### Cost-effectiveness

Cost-effectiveness of mADM versus mADM + MBCT will be analyzed in trial 1 and cost-effectiveness of MBCT versus mADM + MBCT will be analyzed in trial 2. A non-parametric bootstrapping method will be used, performing 1000 replications of the original data to produce confidence intervals. Changes in health-related quality of life from baseline will be used to calculate QALYs in each group. Incremental cost-effectiveness will be expressed in terms of incremental costs per QALY gained. A cost-acceptability curve will be constructed for statistical analysis of the incremental cost-effectiveness ratio. In case of dominance a full cost analysis will be conducted to estimate the mean savings per patient per year. To estimate the long-term consequences of introducing MBCT in the prevention of relapse/recurrence, decision analytic modeling (TreeAge) will be used, comparing mADM, MBCT, and the combination of mADM and MBCT in patients with recurrent depression, over a period of 5 years. Estimates of costs, utilities, and probabilities will be derived from the trial (extrapolation) and, where available, the literature, or from experts. Sensitivity analyses will be conducted to explore sensitivity of the outcomes to various model assumptions.

## Discussion

The prevention of relapse and recurrence in depression is considered a key target in mental health care given the high prevalence of relapse/recurrence of MDD and the accompanying (societal) costs. Previous studies have shown that MBCT significantly reduces the relapse/recurrence risk as compared to treatment as usual [25], but MBCT has not yet been studied as an additional treatment to mADM. Therefore, our first trial will inform health care professionals and patients about the relapse/recurrence risks associated with MBCT in addition to mADM compared with continuing mADM on its own. However, given the large amount of patients who prefer psychological treatment instead of ADM [9] and the difficulties that many patients have with long term use of ADM [7], it seems useful to investigate whether a relatively short, group-based course such as MBCT can help patients taper off their antidepressants. Therefore, our second trial will inform patients and clinicians about the relapse/recurrence risks associated with tapering off mADM after MBCT, compared with continuing mADM after MBCT. This trial is based on non-inferiority because we reasoned that the effectiveness of MBCT on its own (i.e. discontinuing antidepressants after MBCT) should be at least comparable to the effectiveness of mADM on its own. The original study design was an RCT comparing mADM, MBCT, and mADM + MBCT. However, because of the strong treatment preferences that patients expressed during the beginning of the recruitment phase which hampered the randomization possibilities, we adapted our design. Instead of a direct comparison between the three treatment options (three-way randomization) we now allocate the patients to different RCTs based on their preference for either mADM (allocation between mADM and mADM + MBCT) or for MBCT (allocation between MBCT and mADM + MBCT). A methodological consequence of this adaptation is that we cannot directly compare MBCT to mADM because the MBCT preference group may differ from the mADM preference group with respect to known as well as unknown variables. The advantage that comes along with this design however, is an increase in the ecological validity of both trials. In our adapted design, the included patient groups probably more closely reflect the population(s) that we are interested in, since these preferences are obviously present in the population of remitted recurrently depressed adults who use mADM. Moreover, if we had continued using the original three-way randomization procedure, we would have lost all participants who were not willing to be randomly assigned to mADM only or to MBCT only, resulting in a highly selective sample with low generalizability. In summary, more detailed knowledge about the effectiveness of MBCT in addition to mADM, and about MBCT as a possible alternative to mADM is needed. Taking into account patient preferences, the MOMENT study will address these questions to support patients and clinicians in finding the optimal strategy to prevent depressive relapse and recurrence.

## Abbreviations

CSRI: Client Service Receipt Inventory; DSM-IV: Diagnostic and Statistical Manual of Mental Disorders - 4th edition; EQ-5D: EuroQoL-5 Dimensions instrument; FFMQ: Five Facet Mindfulness Questionnaire; IDS-C: Inventory of Depressive Symptomatology – Clinician rating; I-PANAS-SF: International Positive and Negative Affect Scale Short Form; LEIDS-R: Leiden Index of Depression Sensitivity – Revised; MAAS: Mindful Attention Awareness Scale; mADM: Maintenance Antidepressant Medication; MBCT: Mindfulness-Based Cognitive Therapy; MBSR: Mindfulness-Based Stress Reduction; MDD: Major Depressive Disorder; MINI: Mini International Neuropsychiatric Interview; MMAS: Morisky Medication Adherence Scale; NEO-PI-R: NEO Personality Inventory Revised; QALY: Quality Adjusted Life Year; RCT: Randomized Controlled Trial; RRS-EXT: Extended version of the Ruminative Response Scale; SCID-I: Structured Clinical Interview for DSM Disorders-I; SCS: Self Compassion Scale; TAU: Treatment As Usual; WHOQOL: World Health Organization Quality of Life.
